### Statistical Methods

#### Sample Size Calculation

This is a longitudinal study of 150 patients with MS entering the study and predicted to have no more than 20% dropout. Over the study period, we expected 120 patients with MS with longitudinal data for all measured factors: clinical, cellular, and omics. On the basis of CLARITY and CLARITY extension study data, we expect approximately 50% of patients with MS (n=60) to exhibit disease activity according to NEDA 3 (ie, nonresponders) [7-10].

We performed a detailed simulation analysis to assess the power of our sample sizes to detect significant associations at a range of effect sizes and for a range of significance thresholds as per the recommendations of Tsai and Bell [45]. With 120 cases (60 responders vs 60 nonresponders), this study will have 80% power to detect a minimum mean biomarker difference of 10% at a Benjamini-Hochberg false discovery rate of 0.05, which will reasonably balance type I and type II errors. To detect more minor differences, we will use a penalized regression analysis within a machine learning framework using the GLMNet tool [46]. This method is designed for studies with large numbers of predictors and will further enhance the power to identify multi-marker signatures that are predictive of patient response (see details below in the *Association Modeling* section).

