## Introduction

### Overview

Multiple sclerosis (MS) is a common, immune-mediated, demyelinating disease that affects the central nervous system. MS has a highly variable course; therefore, patient-specific treatment decisions are becoming increasingly important. Currently, we have no way to differentiate between the patients who will acquire rapid disability progression and the ones who will remain stable over several years. Most studies point toward early intervention giving a better long-term outcome; however, long-term immunosuppression is associated with increased adverse risk [1,2]. Generally, MS therapies are long-term and some have a demonstrated rebound phenomenon precluding them from being stopped for long periods of time, such as fingolimod [3] and natalizumab [4]. However, there are currently 2 drugs that can potentially be used for immune reconstitution treatment: alemtuzumab and cladribine.

Alemtuzumab is administered in 2 courses, via infusion, 1 year apart. In the Comparison of Alemtuzumab and Rebif Efficacy in Multiple Sclerosis Study (CARE-MS) extension trial, a redosing scheme was introduced, with up to 4 additional doses being offered in the event of recurring clinical activity [5]. Cladribine is a synthetic purine analog, and its mechanism of action is thought to be primarily via induction of apoptosis in lymphocytes [6]. It was shown in a phase III trial (A Safety and Efficacy Study of Oral Cladribine in Subjects with Relapsing-Remitting Multiple Sclerosis; CLARITY) to be highly effective in controlling disease activity [7-10]. With a no evidence of disease activity 3 (NEDA 3) rate of 44% over 2 years [7], it is placed in the range of the most efficacious disease-modifying therapies (DMTs) along with alemtuzumab (39%) [11,12] and ocrelizumab (47%) [13]. Furthermore, after 2 years of treatment and 2 years of follow-up (treatment free), 75% of patients with MS remained relapse free [8,14]. However, clinical stability beyond year 4, and additional doses of cladribine tablets based on clinical activity, has not yet been studied.

In the study discussed below*,* we will offer additional doses of cladribine tablets after 3 years. We aim to compare the clinical outcomes of patients with MS who received additional doses of cladribine with those who changed DMT. We also aim to identify biomarkers for disease control that can be used for treatment decisions, such as redosing with cladribine tablets versus change of DMT.

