There is evidence that clinicians are shifting their treatment goals away from relapse free to achieving NEDA status. For example, a recent study using MSBase data demonstrated that just one new subclinical T2 lesion was associated with 1.62 times odds of changing treatment compared with no new lesions [50]. Patients with MS taking cladribine tablets achieved 47% NEDA 3 rates in CLARITY after 2 years [7]; however, rates of NEDA 4 and data beyond 2 years have not been reported. The addition of accelerated brain volume loss to the NEDA criteria (NEDA 4) is an important parameter as it has been shown to be predictive of long-term disability progression and cognitive decline [26,51]. This is highlighted in the FREEDOM trials, where 31% of patients with MS on fingolimod sustained NEDA 3 status, but only 19.7% achieved NEDA 4 after 2 years [16].

Achieving NEDA status may also differ outside the bounds of RCTs. A real-world study conducted in the USA (MS-MRIUS) evaluated nearly 600 patients with MS on fingolimod and found that NEDA 3 was achieved in approximately 58.7% of patients with MS, and 37.2% had achieved NEDA 4 [52]. The differences may be because of the shorter follow-up time (16 months vs 24 months), different patient populations (less severe disease course), or may be reflective of the real-world nature of the data collection versus an RCT [52]. Another real-world study also reported slightly higher levels of NEDA 3 (44%) after 2 years, but did not evaluate NEDA 4 [53]. There has been one small study of cladribine tablets from MSBase data, which compared outcomes over 1 year [54]. Although this study was shorter than CLARITY, the data were similar, with effects lasting at least 4 years [54] despite the majority of patients with MS receiving only one course of treatment. The MSBase study did not specifically report on NEDA 3 outcomes; therefore, it will be interesting to see if NEDA rates remain the same for cladribine use in the clinical setting.

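### The 60 versus 60 split behind the stated 80% power fits 2-year NEDA-3 rates, but responders are defined at 6 years, so the power is probably overstated for the 6-year biomarker comparison

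*Protocol article*

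**What the plan says.** All references are to the protocol article.

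- **Sample Size Calculation.** The study has "150 patients with MS entering the study and predicted to have no more than 20% dropout", and over the study period "we expected 120 patients with MS with longitudinal data for all measured factors". Citing the phase III trial and its extension, the section continues: "we expect approximately 50% of patients with MS (n=60) to exhibit disease activity according to NEDA 3". No time horizon is attached to the 50%. With 60 responders and 60 nonresponders, "this study will have 80% power to detect a minimum mean biomarker difference of 10% at a Benjamini-Hochberg false discovery rate of 0.05".
- **End Points.** The primary end point is the proportion of patients with NEDA status (the responders) at 6 years relative to screening.
- **Introduction, Overview.** The phase III result is given as "With a no evidence of disease activity 3 (NEDA 3) rate of 44% over 2 years".
- **Discussion, Principal Findings.** The same reference is cited for a 2-year NEDA-3 rate of 47%, and the text adds that "rates of NEDA 4 and data beyond 2 years have not been reported".
- **Association Modeling and the analysis timing that follows it.** Response by NEDA-3 is the dependent variable for the biomarker models. Interim analyses are planned at 24 and 48 months, before the final one.

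**The concern.** Power for comparing two groups of fixed total size depends on how evenly they split. The article assumes an even split at the end of a 6-year study, but its only evidence for that split stops at year 2.

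NEDA-3 means no relapse, no confirmed progression and no new lesion activity. Counted from screening, a patient who loses it cannot regain it, so the responder share can only fall after year 2. If 44-47% hold NEDA-3 at year 2, then 53-56% have already failed. A 50% failure share at year 6 would need no later failures and some reversals as well.

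Finding biomarkers that predict response and the need to redose is a central aim. If the 6-year responder group is well below 60, null biomarker results could be read as coming from a study with 80% power when the power was lower.

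**Working it through.** **1. Counts.** 150 × (1 − 0.20) = 120, and 120 × 0.50 = 60. The article's numbers reproduce exactly.

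**2. The 80% power.** It comes from a simulation whose standard deviation, number of tests and effective per-test threshold are not in the article, so it can be neither reproduced nor refuted. Relative loss can still be shown: take the standardised difference that gives 80% at 60/60, hold it and the total of 120 fixed, and change only the split.

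For a two-sided comparison of two means,

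power ≈ Φ( d / √(1/n₁ + 1/n₂) − z₁₋α/₂ ).

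At α = 0.05 and 60/60: d = (1.960 + 0.842) × √(2/60) = 0.51. A noncentral t calculation gives the same powers to within 0.1 point.

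**3. Year 2, from the article's own rates.**

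- 44%: 0.44 × 120 = 52.8, so 53 vs 67, power 79.5%.
- 47%: 0.47 × 120 = 56.4, so 56 vs 64, power 79.8%.

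At year 2 the departure from an even split costs half a point or less (about 1 point at stricter thresholds).

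**4. Year 6, cumulative from screening.** The article gives no 6-year rate, so the yearly retention r after year 2 is an assumption. Responders = 120 × 0.44 × r⁴.

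| Assumption after year 2 | Share | Split | Power, α = 0.05 | Power, α = 0.001 | Detectable difference relative to 60/60 |
|---|---|---|---|---|---|
| r = 0.95 | 35.8% | 43 vs 77 | 77% | 75% | 1.04 |
| r = 0.90 | 28.9% | 35 vs 85 | 72% | 68% | 1.10 |
| r = 0.85 | 23.0% | 28 vs 92 | 66% | 58% | 1.18 |
| r = 0.80 | 18.0% | 22 vs 98 | 58% | 46% | 1.29 |
| constant rate, 0.44³ | 8.5% | 10 vs 110 | 34% | 16% | 1.81 |

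The last column is √[(1/n₁ + 1/n₂) / (2/60)]. The α = 0.001 column is illustrative; the plan controls a false discovery rate and fixes no per-test threshold.

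Starting from 47% changes little: 0.47 × 0.95⁴ × 120 = 46 responders, 78% power; 0.47³ × 120 = 12 responders, 39% power (α = 0.05).

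**5. What would preserve the claim.** Staying within 2 points of 80% at α = 0.05 needs at least 47 responders (39% of 120). From 44%, that means 47 / 52.8 = 89% of the 2-year responders staying free of disease activity for four more years, or 0.89^(1/4) = 97% per year. In the other direction, at a constant failure rate 50% at 6 years implies 0.5^(1/3) = 79% at 2 years, against the cited 44-47%.

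**The case against.** The strongest reply is that the article says approximately 50%, and 44-47% is approximately 50%. That is right as far as it goes. A reader might infer that the 44% rate contradicts the 60/60 split, but by itself it costs about 1 point of power or less. The problem is the horizon.

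Second, the 6-year rate is unknown. A reader might infer that the responder group will certainly be far smaller and that the stated power will not be reached. The document does not support that certainty. It reports 75% relapse free after 4 years and describes an effect lasting at least 4 years, and patients may be redosed or switched after year 3. The constant-rate case may well be too pessimistic, and at 95% yearly retention the loss is only 3 to 4 points. However, relapse freedom is one of the three NEDA-3 components, so the 75% does not establish a 6-year NEDA-3 rate of 50%.

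Third, the article does not say outright that NEDA is cumulative. Re-baselining after redosing or switching could keep the split nearer even. It is neither stated nor excluded, but the phrase that ties 6-year status to screening points against it. Redosing is also triggered by relapse or new MRI activity, so redosed patients will generally have lost NEDA-3 already.

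Fourth, a journal article may leave the standard deviation and other simulation inputs to the full protocol. That is accepted, and their absence is no part of this point. Nor does the point touch estimation of the primary proportion in this single cohort, which does not depend on the power claim.

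**Conclusion.** The point holds as a mismatch of horizons. The split and the power are printed for the patients expected over the whole study and the responder end point is at 6 years, but the only supporting rates are for 2 years, and the article itself says longer data have not been reported. The arithmetic of the counts is sound.

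If NEDA-3 is cumulative from screening and the cited rates apply to this cohort, 44-47% is a ceiling at 6 years and the 80% is overstated for the 6-year biomarker comparison. The size depends on an assumed retention: about 58-77% power at α = 0.05 for 80-95% yearly retention from 44%, and about 34% at a constant failure rate, with larger losses at stricter thresholds. These are losses relative to an 80% that cannot itself be checked. Re-baselining would weaken the conclusion. At 24 months the stated power is essentially unaffected by the split.

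**What to change.** In Sample Size Calculation:

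1. State the time horizon of the 50% assumption and the expected 6-year NEDA-3 rate with its basis. Say whether NEDA-3 is cumulative from screening or re-baselined after redosing or a switch.
2. Restate power, or the detectable difference, over a range of responder shares, for example 10-45% of 120 (12 to 54 responders). Alternatively, tie the 80% claim explicitly to the planned 24-month analysis, where 53 vs 67 to 56 vs 64 keeps it near 80%.
3. Reconcile the 44% in the Introduction with the 47% in the Discussion, since both cite the same reference for the 2-year rate.

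The cost is re-running the existing simulation with unequal groups, some rewording and a less favourable stated power. Recruitment is complete and no extra patients are needed.

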#### DNA Methylation

Epigenome-wide DNA methylation will be evaluated using DNA extracted from frozen whole blood samples. Genomic DNA will be bisulfite converted and hybridized to Illumina Infinium MethylationEPIC BeadChip arrays at the lead site. Changes in DNA methylation (differentially methylated positions) will be expressed as population medians. Medians will be used to identify changes between responders and nonresponders that meet both the significance cutoff of *P*<.05, and a threshold of >10% change.

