#### Association Modeling

Our primary outcome is treatment response status according to NEDA 3. We will perform parametric statistical analysis to determine whether any clinical parameters are associated with outcome—the dependent variable. Multiple repeated measurements of the same individual will be obtained. Therefore, we will apply generalized linear mixed models for binary outcomes, with random effects for time points to account for within-subject correlations and clustering. Clinical factors included in the primary analysis will be EDSS, MRI, and relapse rate measures regressed at baseline. Confounding factors (age, sex, disease duration, etc) will be included as required. By carefully defining covariate values in terms of lagged or leading indicators of study factors, longitudinal data will help us to establish the direction of causation and any lags involved. We will also use Mendelian randomization techniques to help dissect causation from the correlation of evidence for causality. In this analysis, all predictor biomarker variables will be modeled individually and yield a test-specific (unadjusted) *P* value. However, we will apply a Benjamini-Hochberg false discovery rate to adjust the raw *P* value for multiple testing while maintaining power. The secondary outcome variables will be modeled similarly using mixed models with specific parameters dependent on the type of data.

To identify multi-biomarker signatures that predict response in this patient cohort, we will also use machine learning algorithms on the patient cohort data set. Specifically, elastic-net regularized generalized linear model analyses using logistic, linear, or multinomial or Poisson models (depending on the outcome variable) will be conducted within a cross-validation routine to avoid overfitting. This will be performed on the entire factor set using the GLMNet package in the R program [46]. Briefly, GLMNet fits a generalized linear model via penalized maximum likelihood and is akin to a stepwise forward regression with the added feature of being able to perform internal cross-validation. GLMNet allows for both binary and multinomial outcomes. GLMNet allows for the rapid discovery of reduced factor panels that are likely to be associated with outcomes. This complementary approach is not susceptible to multiple testing burdens and will facilitate the identification of the best fitting multifactor signature that is predictive of treatment response [46].

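### A single claim of 80% power for a 10% difference at FDR 0.05 covers every biomarker, from about 11–20 cell and serum measures to an epigenome-wide array, and is not a property of the design; BH families should be fixed and power stated by class

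*Protocol article*

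**What the plan says.** Protocol article, Sample Size Calculation: the sample is "150 patients with MS entering the study and predicted to have no more than 20% dropout", which leaves 120, and "we expect approximately 50% of patients with MS (n=60) to exhibit disease activity according to NEDA 3". The power statement is "With 120 cases (60 responders vs 60 nonresponders), this study will have 80% power to detect a minimum mean biomarker difference of 10" (the figure is 10%), at a BH false discovery rate of 0.05. The section says a simulation covered ranges of effect size and significance threshold. It gives no SD, no scale for the 10% and no number of tests. It describes the data as clinical, cell-based and omics.

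Association Modeling: "all predictor biomarker variables will be modeled individually and yield a test-specific (unadjusted) *P* value", and then "we will apply a Benjamini-Hochberg false discovery rate to adjust the raw *P* value for multiple testing while maintaining power". No classes of predictor are named.

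DNA Methylation: "Epigenome-wide DNA methylation will be evaluated using DNA extracted from frozen whole blood samples". Positions are selected by P<.05 together with a change above 10%; no FDR is mentioned.

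Lymphocyte Subsets, Table 1: six rows in the TBNK panel and five in the B memory panel, with absolute and proportional values ticked separately. Serum NfL is a further single measure.

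**The concern.** Power for a 10% mean difference depends on the marker's SD and on the P value it must reach. Under BH, that P value depends on how many tests share the adjustment and how many of the others are positive. The predictors differ greatly in both respects, so one power figure cannot describe them all.

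The consequence is one of interpretation. The article proposes serum NfL as a possible indicator of the need for further courses, and blood biomarkers generally as predictors of response and redosing. A null result for such a marker would be read against a stated 80% power that may not apply to it. If the BH run is pooled, whether a cell or serum marker is declared positive would also depend on how many unrelated methylation positions happen to differ.

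**Working it through.** **Inputs from the article.** 60 v 60; 80% power; 10% mean difference; BH FDR 0.05. The sample flow reproduces: 150 × 0.80 = 120, and half of that is 60.

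**Number of cell and serum measures.** Table 1 has 6 + 5 = 11 rows. Counting absolute and proportional values separately gives 12 (TBNK) + 7 (B memory) = 19, and serum NfL makes 20. The range used is 11–20.

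**Assumptions.** Two-sided, two-sample comparison at one time point; 10% taken relative to the mean (if it means percentage points, the same limits apply to the SD in points); array size 10^4 to 8×10^5 tests, or 850,000 in the pooled simulation; independent tests. The article gives none of these.

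**The stated 80%.** It cannot be recomputed without an SD and a number of tests. It can be solved for the SD that would make it true.

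**Step 1. Detectable difference d, in SD units.** With n = 60 per group, the normal approximation is d = (z for α/2 + z for 80%) / √(60/2), where √30 = 5.477. At α = 0.05, d = (1.960 + 0.842)/5.477 = 0.511; the noncentral t with 118 df gives 0.516. BH compares the k-th smallest of m P values with 0.05k/m, so a lone true marker must reach about 0.05/m. The largest SD/mean for a 10% difference is 0.10/d. The d and SD/mean columns use the noncentral t.

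| Tests m | Threshold 0.05/m | d for 80% power | Largest SD/mean |
|---|---|---|---|
| 1 (unadjusted) | 0.05 | 0.516 | 19.4% |
| 11 | 0.0045 | 0.683 | 14.6% |
| 20 | 0.0025 | 0.720 | 13.9% |
| 10^4 | 5×10^-6 | 1.033 | 9.7% |
| 8×10^5 | 6.25×10^-8 | 1.217 | 8.2% |

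**Step 2. The spread alone.** If the SD were 30% or 50% of the mean (assumed), power for a 10% difference would be 44% or 19% at an unadjusted 0.05, and 15% or 4% in a family of 11. No pooling is involved.

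**Step 3. Pooling.** Take d = 0.68, which has about 80% power in a family of 12 with one true marker (81% in simulation). Pool those 12, three of them truly different, with 850,000 positions, where the true positions differ by 1.0 SD. A small simulation (60 runs per row, normal approximation) gives:

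| Truly different positions | Power for the d = 0.68 marker |
|---|---|
| 0 | 3% |
| 85 | 16% |
| 850 | 35% |
| 8,500 | 62% |
| 85,000 | 82% |

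**Step 4. Error rate within the small class.** With 85,000 of 850,000 positions true (10%), nearly all are rejected, so the pooled BH cutoff settles near 0.05 × (0.9 × 0.0052 + 0.1 × 0.996) ≈ 0.0052. If no marker in the small class is truly associated, every rejection there is false, and the chance of at least one is 1 − (1 − 0.0052)^12 = 6.1% for 12 markers and 9.9% for 20. The pooled run therefore does not guarantee 5% within that class. If several of its markers are true, the rate can be below 5%.

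**Step 5. The methylation rule.** If its P<.05 is unadjusted, 850,000 null positions would yield 0.05 × 850,000 = 42,500 with P<.05 before the filter on size of change. That is a different procedure from BH at 0.05.

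**The case against.** The strongest objection is that pooling is inferred. Association Modeling does not say that cell, serum and methylation tests share one BH run, and the separate methylation rule points the other way. Forming families is often left to the SAP, which is not shown. This stands in part: pooling is the plain reading but is not stated, so every pooled figure above is conditional. The article does, however, itself fix a multiplicity rule and a power figure, and Steps 1 and 2 need no pooling.

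A reader might infer that one threshold cannot give 80% power to both kinds of marker. That is true for a common standardized difference, but the article states a raw 10%. If every marker had an SD of about 8% of its mean or less, 80% would be reached at both thresholds. The figure is unsupported as a general claim; it is not shown to be impossible.

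A reader might also infer that serum NfL and lymphocyte markers are left with almost no power. That holds only if BH is pooled, few positions truly differ, and the marker's spread is not small. BH adapts, and Step 3 runs up to 82%.

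Two further points stand. The planned analysis uses mixed models on repeated measurements, not a single-time-point t test, so the values of d are a guide. Elastic-net on the full factor set offers a second route that applies no BH cutoff. Neither makes the quoted sentence true of all markers. The 10% may have been meant for methylation, whose own threshold is also 10%; if so, the sentence should say so.

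**Conclusion.** The concern holds in a limited form. The single statement of 80% power for 10% at FDR 0.05 is not a property of this design across the markers it covers. With sparse signals it requires an SD of at most about 14–15% of the mean for a family of 11–20 and 8–10% for the array, and the article states no SD. The detectable standardized difference is about 1.4 to 1.8 times as large on the array as in the small class (1.033/0.720 = 1.43; 1.217/0.683 = 1.78).

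Under a pooled BH run, power for a cell or serum marker would be set largely by the methylation results. The documents do not establish that the run is pooled or that signals are sparse, so near-zero power is the unfavourable end of a range. The mismatch between the methylation selection rule and the BH rule is visible in the text and needs no assumption. The point merits a change to the plan. It does not invalidate the study.

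**What to change.** 1. **Association Modeling:** apply BH at 0.05 separately within prespecified classes, at least (a) lymphocyte subsets with serum NfL and (b) methylation positions. List the members of (a), saying whether absolute and proportional values count separately. MRI is named there as a clinical factor in the primary analysis, so it should not become a biomarker class by default.

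2. **DNA Methylation:** reconcile the P<.05 plus above-10% rule with BH, for example by stating that the P value meant is the BH-adjusted one within the methylation class.

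3. **Sample Size Calculation:** limit the 80%-for-10% sentence to the marker class, scale, SD and number of tests used in the simulation. Add detectable standardized differences by class, for example about 0.68–0.72 SD for 11–20 markers and about 1.0–1.2 SD for the array. Label these as conditional on a two-sample comparison, sparse signals and the number of positions tested.

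The cost is wording and a restated power figure, with no new data or patients. The stated power becomes less favourable, and FDR is controlled per class and no longer over one combined list. The classes should be fixed before the biomarker results are examined, so that the choice cannot follow the data.
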